#### Facilitator training and distress management

Research facilitators will be trained in ACP principles and familiarised with recent changes to legislation with the introduction of the Medical Treatment Planning and Decision Act 2016 [31]. They will additionally be familiarised with ACP and the specificities of the appointment of an MTDM and completion of Instructional and Values Directives. Given that the video vignettes may potentially elicit distress in participants, research facilitators will also be trained on how to respond to distress and procedures around seeking additional support for participants. Researchers will be advised to offer to discontinue the video if deemed appropriate.

#### Data monitoring and confidentiality

Research facilitators will be asked to complete field notes as part of the study monitoring plan. The project team will meet monthly to review the progress of the study. Adherence to the research protocol will be monitored throughout the study. Protocol violations or operational issues will be discussed and resolved at project team meetings. The study steering committee will monitor the study and provide ongoing oversight into early results. If necessary, modifications to the study will be made. To ensure confidentiality, data will be stored in a secure database. Information and measurements will be stored independently from identifiable personal information.

### Study arms

#### Usual care

Patient-caregiver dyads will be provided with a verbal explanation of ACP, an ACP document, and verbal and written guidelines on how to complete the document. Questions will be fielded, and finally, participants will be provided with the patient and caregiver post-questionnaires to be completed individually and returned with the completed ACP in a stamped return envelope.

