**Fig. 1 Fig1:**
[figure not shown]
Study procedure

Patients and caregivers will be consented individually by the research facilitator and will complete individual baseline pre-questionnaires (Supplementary file). Participants will then be randomised as dyads to either the UC or VDST arm. All participants will be advised that participation is voluntary, they may withdraw at any time, and that all information gathered will be treated in the strictest confidence. Patients and caregivers will also be advised that non-participation will not affect their care or their choice to complete an ACP.

Patients from both groups will be advised to discuss their completed ACP with their general practitioner or treating specialist to clarify any questions. The completed ACP will have to be signed, witnessed and returned with the post-questionnaire in a stamped return envelope. Participants will be advised to return the questionnaires even if they choose not to complete the ACP. Participants will receive two telephone call prompts at two-week intervals on completion of the intervention as a reminder to return the completed documents. Returned ACP’s will be scanned into the hospital’s electronic record system, and a copy returned to the patient.

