### Sample size and power

Based on the primary outcome of the completion of ACP documentation and assuming a completion rate of around 37% for the control group, with a total of 86 participants/dyads (43 per group) we will be able to show a significant improvement to 67% completion for the VDST group (power of 80%, two sided 5% significance level). Assuming an estimated dropout rate of 30%, recruitment of 112 dyads will be required. Based on previous published studies, we felt that a sample of this size would give us sufficient methodological experience to conduct a subsequent fully powered study [12].

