#### VDST group

Participants randomised to the VDST group will be shown the video on a mobile computer. The video will be viewed by patient-caregiver dyads simultaneously. Research facilitators will offer to discontinue the video at any point if it elicits distress. Following this, the participants will be provided with a verbal explanation of ACP and be provided with the hospital’s ACP document, and verbal and written guidelines on how to complete the document. Questions will be fielded, and finally, participants will be provided with patient and caregiver post-questionnaires to be completed individually and returned with the completed ACP in a stamped return envelope.

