#### Data collected and measures used

Table 3 outlines the measures used at baseline and post-intervention. The baseline questionnaire will include the patient’s and caregiver’s demographic information, including age, sex, marital status, place of birth, the relationship between patient and caregiver, primary cancer diagnosis, and length of time living with the diagnosis. Patients will be asked if they had previously discussed prognosis with their doctor.

**Table 3 Tab3:** Measures used pre and post UC and VDST

Measures used	Patient		Caregiver	
	Baseline: Pre UC/VDST	Post UC/VDST	Baseline: Pre UC/VDST	Post-UC/VDST
Demographics	**×**		**×**	
DASS-21	**×**			
ACP Attitudes	**×**	**×**	**×**	**×**
CCAT	**×**	**×**	**×**	**×**
PDMS	**×**	**×**	**×**	**×**

*DASS-21* Depression, Anxiety and Stress Scale, *CCAT* Cancer Communication and Assessment Tool, *PDMS* Preparation for Decision Making Scale

The following variables and outcomes will be assessed:

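### The post-questionnaire shares an envelope with the signed ACP, so return and timing of the secondary outcomes may depend on the primary outcome and may differ by arm

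*Protocol article*

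**What the plan says.** The return route is stated three times in the Protocol article, and it is the same in both arms. Under Usual care, the patient and caregiver forms are "to be completed individually and returned with the completed ACP in a stamped return envelope". Under VDST group, "participants will be provided with patient and caregiver post-questionnaires to be completed individually and returned with the completed ACP in a stamped return envelope". Under Study procedures, "The completed ACP will have to be signed, witnessed and returned with the post-questionnaire in a stamped return envelope". Patients are also advised, but not required, to talk the completed ACP through with a general practitioner or specialist.

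Two safeguards appear under Study procedures. The first is "Participants will be advised to return the questionnaires even if they choose not to complete the ACP". The second is "Participants will receive two telephone call prompts at two-week intervals on completion of the intervention as a reminder to return the completed documents".

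The primary outcome is completion of ACP documentation (Outcome assessment). Attitudes, CCAT and PDMS are all measured by questionnaire, before and after the intervention, in patients and caregivers. On timing, "Table 3 outlines the measures used at baseline and post-intervention", and the column head of that table says only that the second measurement follows usual care (UC) or the video (VDST). The text shown gives no due date for the form.

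**The concern.** The form that carries every secondary outcome travels with the document that defines the primary outcome. The only source of completion data that the article describes is the returned ACP. A dyad counted as a completer has therefore posted the envelope in which the questionnaire is also due. A dyad that is still deciding, or is waiting for a signature or a witness, has a practical reason to keep the whole envelope.

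The trial plans a 30-point arm difference in completion. If return depends on completion, the arms may then differ in how many questionnaires come back, from whom, and how long after the visit. The Statistical analysis section compares changes from before to after the intervention between groups, and a change needs a returned second form. Timing matters most for the PDMS, which rates how useful the intervention was: an answer given soon after the visit may differ from one given weeks later, after other conversations. What is at stake is the reading of the secondary comparisons. The primary comparison is not touched by this point.

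**Working it through.** **Inputs from the Protocol article (Sample size and power; Randomization and blinding).** Completion 37% in UC and 67% in VDST; 80% power, two-sided 5%; 43 per group; 30% dropout; 112 dyads at 1:1, so 56 per arm.

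**Inputs not in the documents.** The questionnaire return rate among ACP completers (rc) and among non-completers (rn). Both are assumed below, with a range.

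**1. The plan's own figure.** Mean completion is (0.37 + 0.67)/2 = 0.52. With pooled variance and no continuity correction,
n = [1.96·√(2·0.52·0.48) + 0.8416·√(0.37·0.63 + 0.67·0.33)]² / 0.30² = 42.3, so 43 per group. Power at 43 is 80.6%. The stated 86 reproduces, so 37% and 67% are the planning values to use.

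**2. Return by arm.**
UC: 0.37·rc + 0.63·rn. VDST: 0.67·rc + 0.33·rn. Difference (VDST minus UC): 0.30·(rc − rn).

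| rc | rn | UC return | VDST return | Difference |
|---|---|---|---|---|
| 0.90 | 0.90 | 90.0% | 90.0% | 0 points |
| 0.90 | 0.80 | 83.7% | 86.7% | 3 points |
| 0.90 | 0.70 | 77.4% | 83.4% | 6 points |
| 0.90 | 0.50 | 64.8% | 76.8% | 12 points |
| 1.00 | 0.00 | 37.0% | 67.0% | 30 points (extreme) |

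**3. Fixing overall non-return at 30%.** This reads the planned dropout as questionnaire non-return, which is an assumption. Non-return among non-completers is (0.30 − 0.52·(1 − rc))/0.48.

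- All completers return: 0.30/0.48 = 0.625. Missing is 0.63·0.625 = 39.4% in UC and 0.33·0.625 = 20.6% in VDST, about 22 and 12 of 56 dyads. This is the upper case for a 30% total.
- 90% of completers return: (0.30 − 0.052)/0.48 = 0.517. Missing is 0.037 + 0.63·0.517 = 36% in UC and 0.067 + 0.33·0.517 = 24% in VDST.
- 80% of completers return: (0.30 − 0.104)/0.48 = 0.408. Missing is 0.074 + 0.63·0.408 = 33% in UC and 0.134 + 0.33·0.408 = 27% in VDST.

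**4. Shift in a secondary comparison.** Assume that non-returners score 0.5 SD worse than returners in both arms. Each arm's observed mean is then too good by 0.5 times its missing share, and the arm difference moves by 0.5 times the difference in missing shares.

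- Upper case: 0.5·(0.394 − 0.206) = 0.094 SD.
- 80% of completers returning: 0.5·(0.331 − 0.269) = 0.031 SD.
- Return differences of 3 to 12 points (step 2): 0.015 to 0.06 SD.

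More is missing in UC, so UC looks better than it should, and the video effect is understated.

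**5. Size against sampling error.** In the upper case 34 and 44 dyads return. The standard error of a standardised difference is about √(1/34 + 1/44) = 0.23, so 0.094 SD is about 0.4 standard errors.

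**The case against.** The strongest reply is that the plan already addresses the risk. Dyads are told to return the form without an ACP, and both arms get the same two prompts. If that works fully, rc equals rn and the arm difference in return is zero whatever the completion rates. This stands as a reason to write may rather than will. It does not dispose of the point: the advice is aimed at dyads who decline an ACP more than at those still undecided or waiting for a witness, and the prompts set no cut-off.

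A reader might infer that missing data will certainly depend on completion and differ by arm. The documents do not support that, because they give no return rate by completion status. A reader might also take 39% against 21% as the plan's own figures. They are not. The 30% is a dropout allowance on the primary-outcome sample size, and the Limitations section links attrition to illness and death, which need not follow ACP completion. Nor does the text say that completers fill in the form after seeing a doctor: that discussion is only advised, and signing and witnessing govern posting, not when the answers are written.

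It is also fair that the article is condensed and its study-procedure figure is not shown, so a due date may exist elsewhere. The shared envelope, however, is a stated procedure and not an omitted detail. Finally, the shift is small against sampling error, works against the video under the stated assumption, and concerns secondary outcomes of an exploratory pilot. All of that stands and limits the weight of the point.

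**Conclusion.** The point holds as a risk and not as a certainty. One envelope ties every secondary outcome to the primary outcome, so missingness and timing may depend on ACP completion and, if the video raises completion, may differ by arm despite the advice and the prompts.

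The size depends on one unknown, the return gap between completers and non-completers. The arm difference in return is 0.30 times that gap: nothing with no gap, and 3 to 12 points for assumed gaps of 10 to 40 points. The case of 39% against 21% missing, with its shift of about 0.09 SD, is an assumed upper case. It needs the 30% dropout to be questionnaire non-return that falls only on non-completers, together with a 0.5 SD difference between non-returners and returners. If non-returners score worse, the shift hides part of a video benefit and does not create one. This is an optional improvement worth making because it costs so little.

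**What to change.** Return the questionnaire separately from the ACP:

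- Give each dyad a second stamped envelope for the two post-questionnaires. Mark it with the dyad's study code, since the Abstract calls the questionnaire anonymous and each form must still be linked to its baseline and to ACP status.
- Set one fixed due date, the same in both arms, for example the date of the first telephone prompt.
- Ask for the completion date on each form.
- Have the first prompt ask for the questionnaire whether or not the ACP is finished.
- Report return rates by arm and by ACP completion.

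The cost is one more stamped envelope per dyad, a date line on the form and one line in the call script. The intervention and the primary outcome stay as they are. The downside is that some forms will be completed before the ACP is signed, but timing then becomes alike in both arms. A questionnaire that arrives with no later ACP still shows a dyad that was in contact, although it no longer separates a decliner from a dyad lost after the due date.

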#### VDST group

Participants randomised to the VDST group will be shown the video on a mobile computer. The video will be viewed by patient-caregiver dyads simultaneously. Research facilitators will offer to discontinue the video at any point if it elicits distress. Following this, the participants will be provided with a verbal explanation of ACP and be provided with the hospital’s ACP document, and verbal and written guidelines on how to complete the document. Questions will be fielded, and finally, participants will be provided with patient and caregiver post-questionnaires to be completed individually and returned with the completed ACP in a stamped return envelope.

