### Study procedures

The study procedure is shown in Fig. 1. Participating clinicians will screen patients for eligibility, and interested eligible patients will be asked to nominate a participating caregiver. Eligible dyads will be informed verbally and in writing about the study and will be invited to meet with a research facilitator in their own homes or an allocated room in the hospital at an assigned date and time.

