*Baseline Depression, Anxiety and Stress scores*. The DASS 21 scale is a validated 21 item self-reported questionnaire designed to measure the negative emotional states of depression, anxiety, and stress [35]. Evaluation of the DASS 21 in cancer has shown acceptable internal consistency reliability for the Depression subscale (α = .90) and Anxiety subscale (α = .70) with construct validity to measures of suicidal ideation, quality of life, self-rated health, and depressed mood [36].*Attitudes towards ACP*. Understanding of, opportunities, distress, and confidence related to ACP will be assessed using a previously designed and tested questionnaire comprising nine patient and eight caregiver items, measured on a 10 point Likert scale [32].*Congruence in decision-making* will be measured using the Cancer Communication Assessment Tool for Patients and Families (CCAT-PF). CCAT-PF consists of 18 items and measures congruence in patient-caregiver communication with the analogous patient (CCAT-P) and family (CCAT-F) instruments, exploring preferences, values, and experiences in treatment decision-making. The CCAT-PF demonstrated internal reliability coefficients for the CCAT-P (α = .52), CCAT-F (α = .50), and CCAT-PF (α = .60). Higher CCAT-PF scores are significantly correlated with greater patient depression and perceived family conflict, lower patient-caregiver assessment and well-being, and less expressiveness and family cohesion [37].*Preparation for decision-making* will be measured using the Preparation for decision-making scale, a validated scale assessing patient and caregiver perception of an intervention’s usefulness. Psychometric analysis has shown Alpha coefficients for internal consistency ranging from 0.92 to 0.96 and that the scale discriminated significantly between patients who did and did not find a decision aid helpful (*p* < 0.0001) [38].

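### Both post-questionnaires leave with the dyad for postal return, so the independence of patient and caregiver answers behind the CCAT-PF congruence outcome rests on an instruction alone

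*Protocol article*

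**What the plan says.** Congruence in communication is one of three secondary outcomes (Protocol article, Outcome assessment). It is measured with the 18-item CCAT-PF, which "measures congruence in patient-caregiver communication with the analogous patient (CCAT-P) and family (CCAT-F) instruments" (Data collected and measures used). Table 3 has both members of the dyad complete it before and after the intervention.

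Baseline forms belong to the facilitator meeting, before randomisation: "Patients and caregivers will be consented individually by the research facilitator and will complete individual baseline pre-questionnaires" (Study procedures). Dyads are "invited to meet with a research facilitator in their own homes or an allocated room in the hospital".

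The post-intervention forms are handed over at the end of the session. For the VDST arm the text is "participants will be provided with patient and caregiver post-questionnaires to be completed individually and returned with the completed ACP in a stamped return envelope"; for usual care it is "participants will be provided with the patient and caregiver post-questionnaires to be completed individually and returned with the completed ACP in a stamped return envelope". Study procedures repeats the return route: "The completed ACP will have to be signed, witnessed and returned with the post-questionnaire in a stamped return envelope". It adds: "Participants will receive two telephone call prompts at two-week intervals on completion of the intervention as a reminder to return the completed documents".

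The Statistical analysis section compares secondary outcomes between the two groups on pre-to-post change.

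**The concern.** A score built from two people's answers to analogous items measures agreement only if each person answers without the other. After the intervention both forms leave with the dyad and may be outstanding for weeks. They come back with the one document the pair has in common, the patient's ACP. Nothing in the described procedure stops one member reading the other's form when the packet is put together, or the two settling on shared answers.

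Two things could follow. Discordance could fall after the session because of how the forms were filled in rather than how the pair communicates. And people may soften answers that the other could read: the attitude items cover distress and confidence, and CCAT-PF is described as correlating with perceived family conflict.

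The protocol says that earlier VDST trials did not examine patient-caregiver communication, and the pilot is meant to inform a multisite study. As described, the procedure gives no means of telling better communication from shared form-filling.

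**Working it through.** **1. The two measurement occasions side by side**

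| | Baseline | Post-intervention |
|---|---|---|
| When | At the facilitator meeting, before randomisation | After the session; reminder calls at two-week intervals |
| Where | Home or hospital room | Not stated; postal return implies away from the facilitator |
| Stated safeguard | Individual forms | Forms to be completed individually |
| Return | Not described as postal | With the ACP, in a stamped envelope (singular) |
| Differs by arm? | No | No |

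Completion at home, completion unsupervised and a single shared envelope are inferences from postal return, the reminder calls and the singular article. They are not stated.

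**2. Direction.** Higher CCAT-PF scores are described as going with worse dyad functioning, so artificial agreement would appear as a lower score.

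**3. Inputs.** The documents give 37% v 67% completion, 80% power, two-sided 5%, 43 dyads per group, 30% dropout and 112 recruited. The two-proportion formula (pooled variance, no continuity correction) reproduces 43 per group, with power 80.6%. These figures only supply a group size here. The documents give no CCAT-PF mean or SD and no conferring rate, so every other input below is an assumption.

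**4. Equal conferring in both arms.** If a share *c* of dyads confers and conferring shrinks a dyad's discordance by a fraction *s*, the expected artificial change is −*c* × *s* × mean. With an assumed mean of 18:

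- *c* = 0.30, *s* = 0.25: −0.30 × 0.25 × 18 = −1.35 points
- *c* = 0.50, *s* = 0.50: −0.50 × 0.50 × 18 = −4.50 points

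This was simulated with no true effect: 20,000 trials per scenario, 43 dyads per arm, SD 6, pre-post correlation 0.5, and a two-sample *t*-test on change. The between-arm false-positive rate stayed at 5.0%. A within-arm pre-post test was significant in 28% to 98% of trials. If conferring is unrelated to the score, a true difference in post scores is multiplied by 1 − *c* × *s*, that is 0.925 to 0.75 in these two cases.

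**5. Unequal conferring.** Same simulation, *s* of 25% and then 50%:

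| Conferring, UC v VDST | Between-arm false-positive rate |
|---|---|
| 20% v 40% | 10.4%, 21.7% |
| 20% v 50% | 17.3%, 42.2% |
| 10% v 50% | 27.2%, 66.8% |

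A milder closed-form case assumes a gap of 20 percentage points and shrinkage of 30%: 0.20 × 0.30 = 6% of the mean. If the mean is 2, 3 or 4 SDs, the false difference δ is 0.12, 0.18 or 0.24 SD. With *n* = 112 × 0.70 / 2 ≈ 39 per arm and √(39/2) = 4.416, the rejection probability is Φ(4.416δ − 1.96) + Φ(−4.416δ − 1.96):

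- δ = 0.12: 0.083
- δ = 0.18: 0.125
- δ = 0.24: 0.185

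The results run from 5.0% to about 67%, depending almost wholly on an unknown difference in conferring between arms.

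**The case against.** The strongest reply is that randomisation handles most of this. The return procedure is the same in both arms and the planned comparison is between arms, so a common change in measurement conditions cancels in expectation. That stands, and step 4 of the working confirms it.

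The protocol also requires individual completion, and any self-completed postal questionnaire relies on such an instruction. Envelope counts and wording printed on forms are detail that an article may leave to the full protocol, and the questionnaire itself is in a supplementary file. This also has force: nothing is contradicted. But the return route is a stated procedure, given in three places, and for a paired-agreement score it is weaker than it need be.

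The contrast with baseline should not be pressed far. Baseline may also take place in the dyad's home, and the text does not say that the facilitator separates the pair or watches completion.

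A reader might infer that the between-arm congruence result is biased in favour of the video. The documents do not support that. Dyads in the VDST arm watch together a video that models dyad conversation, in an open-label trial, so more joint completion there is plausible. But usual-care dyads also receive a joint explanation, the same kind of ACP document and the same forms. No passage shows a difference in conferring.

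**Conclusion.** The point holds in a limited form. CCAT-PF needs independent answers, both post forms leave with the dyad and return with the ACP, and the only stated protection is the instruction to complete them individually. Conferring or reading the other's answers is therefore possible, and could lower measured discordance and reduce candour.

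The main exposure is pre-to-post change within each arm, with some blunting of a true difference. Bias in the planned between-arm comparison requires conferring to differ by arm, which is plausible but unproven. Its size cannot be estimated from the documents, and the calculated rates show what would follow under assumed inputs, not what is expected. The primary outcome, ACP completion, does not depend on these answers. This is a cheap improvement to a secondary outcome in a pilot, not a fault in the trial's main inference.

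**What to change.** In the Usual care and VDST group sections, and in the matching sentence of Study procedures, specify the following identically for both arms:

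- Give the patient and the caregiver each a coded, sealable envelope for the post-questionnaire. The person who completed the form seals it, and both go into the common prepaid return envelope with the ACP. Two separate mailings would risk one form returning without the other, leaving no CCAT-PF score for that dyad.
- Instruct on each form that it be completed alone, before answers are discussed.
- Add one item asking whether the form was discussed or completed with the other person.

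In the Statistical analysis section, keep all randomised dyads with data in the main congruence comparison and report the frequency of joint completion by arm. Label any analysis that excludes dyads reporting joint completion as a descriptive sensitivity analysis. It conditions on behaviour after randomisation and, if conferring differs by arm, would remove dyads unevenly.

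The cost is two inner envelopes per dyad, one added item and slightly more handling. Sealing stops one person reading the other's form at packing but does not fully prevent conferring. The added item shows how often that is reported.
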